### Objectives

The primary objective of the Breastfeeding Trial is to assess the effect of a community-based breastfeeding support programme delivered by health visitors in primary healthcare on the duration of exclusive breastfeeding and social inequality in breastfeeding among women in Denmark. Our hypothesis is that women who receive strengthened breastfeeding support in conjunction with the breastfeeding support offered in the hospital setting will overcome breastfeeding challenges and therefore breastfeed exclusively for a longer period of time. We anticipate that by administering a higher dose of the intervention to mothers who are young or have a low educational attainment, the effects will be even stronger in this group, thereby reducing social inequality in breastfeeding.

We will conduct a comprehensive, multidisciplinary evaluation of the trial by investigating whether the present complex intervention is effective compared with usual breastfeeding support, with respect to:The proportion of women who are breastfeeding exclusively at four months postpartumThe overall duration of exclusive breastfeedingReducing social inequality in breastfeeding

In a process evaluation, we investigate the processes of implementation, specifically:Facilitators of and barriers to implementing the interventionDose, delivery and fidelity of the interventionHow the training programme affects health visitors’ knowledge, self-efficacy and action competencies regarding breastfeeding support

Using a realist evaluation approach, we investigate the relationship between context, mechanisms and outcomes to determine *whether* and *how* the intervention works. The realist evaluation will focus primarily on families in which the mother is young or holds a low educational attainment (i.e., the group that will receive an intensified version of the intervention (see a description of the intervention in Table 2)). More specifically, we will:Investigate important mechanisms of change by examining families and health visitors’ response to and interaction with the interventionAnalyse how contextual factors promote or inhibit the implementation process and the expected mechanisms of change and the potential consequencesInvestigate how the intervention works for mothers who are at an increased risk of early breastfeeding cessation

Finally, in a health economic evaluation, we will assess:The cost-effectiveness of the interventionThe cost-utility of the intervention

### Definitions

In this trial, exclusive breastfeeding means that the infant exclusively receives breast milk after discharge from the hospital, regardless of feeding mode. In Denmark, and hence in this trial, exclusive breastfeeding allows for supplementing with, e.g., water and/or a maximum of one meal of infant formula per week [7]. Partial breastfeeding means that, in addition to breast milk, the baby receives infant formula or other diet elements several times a week or daily.

## Methods and analysis

### Study design

The Breastfeeding Trial is a cluster-randomised trial with two arms: an intervention and a control arm. As the developed programme constitutes a complex intervention, we adhere to the Medical Research Council (MRC) framework and wish to combine the effectiveness perspective with a theory-driven evaluation, analysing how the activities generate effects to provide comprehensive evidence for decision making [32].

We use survey data to reveal any effect on the outcome of exclusive breastfeeding at four months postpartum. Consequently, this study protocol reports on the survey study in accordance with the SPIRIT Statement [33]. Additionally, a register-based difference-in-difference study and a process-, realist- and health economic evaluation will be conducted as part of the trial. We have included information about these methodologies in the current study protocol. The integration and design of the various aspects of investigation are guided by a programme theory that depicts in a logic model frame how the activities of the intervention are expected to produce outcomes (see Fig. 2).

We analyse the effect of the intervention between the trial arms by harvesting data from continuous monitoring of breastfeeding duration in nation-wide registries [34]. In a process evaluation [35], we assess the fidelity and quality of the implementation of the intervention (dose, adaptations and reach) and identify contextual factors potentially associated with variation in outcomes. Furthermore, the intervention mechanisms will be analysed using a realist approach [36, 37] in the intervention arm to understand how intervention activities and resources in the specific contexts potentially generate mechanisms and outcomes, with special focus on families with a low SEP. Finally, a health economic assessment will be conducted using cost-effectiveness and cost-utility approaches [38].

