### Study population

The study setting includes 21 municipalities in Denmark, all of which are situated in the North Denmark Region (*n* = 6) or Region of Southern Denmark (*n* = 15) (see Fig. 1). Denmark consists of a total of five regions. The two selected regions have some of the highest proportions of mothers who are of young age and/or have a low educational attainment. Each of the 21 participating municipalities constitutes a cluster in the trial.

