**Development and implementation**
For the adaptation of the previous successful breastfeeding intervention done by Nilsson and colleagues (2017) in hospital setting, an assessment of the needs of families following discharge from hospital after birth and until six months postpartum was carried out. Programme objectives corresponding to findings from the needs assessment formed the basis of the adaptation. In the adaptation process, a participatory approach including health visitor representatives from each of the intervention municipalities was chosen to enhance ownership, to match the organisational structure of the setting (the Danish Health visiting programme), and to ensure implementation in the intervention municipalities. The final intervention programme consisted of a breastfeeding programme for parents and a related training programme for health visitors. In December 2021, 210 health visitors from the 11 intervention municipalities completed a preparatory 3.5-h e-learning course, and in March 2022 they participated in the 15-h physical attendance interactive training programme supported by a written manual. Following training, the health visitors immediately initiated implementation of the programme in their municipalities

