#### Randomisation

The participating municipalities were randomised for either the intervention or control arm by a statistician using computer-generated cluster randomisation. Randomisation was stratified by Danish region and number of annual births per municipality (0 =  < 900, 1 = 900 +). The number of annual births in a municipality was associated with maternal educational level and age as urban cities with more inhabitants and thus more births had fewer mothers with a low educational level and young age than rural districts with fewer births. Stratification of randomisation was performed to increase the exchangeability of the two trial arms.

The intervention works by strengthening competencies at health visitor level. Once achieved, such competencies are difficult and unethical not to use, wherefore randomisation at the level of families was discarded. Randomising at the cluster level serves to mitigate the risk of contamination between trial arms. Allocation to the intervention or the control arm is based on address and municipal affiliation.

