### Multidisciplinary evaluation data

#### Difference-in-Difference design using register data

In the National Child Health Register, municipalities have been required to report data on exclusive breastfeeding since 2011. Difference-in-difference analyses will be applied to estimate the difference in change in proportions breastfeeding at four months, and in average number of weeks of breastfeeding from before (≤ 2021) to after (≥ 2022) the intervention period comparing the intervention and control arm. The advantage of this approach is that it will provide an estimate of the effect if treatment is upscaled to the entire country. The effect of the intensified intervention in the difference-in-difference analyses will be examined by including an interaction term like in the survey analyses. Data from national Danish registers will be retrieved on all mother–child dyads in the included 21 municipalities from 2015 to 2025. This part of the evaluation awaits data availability in the registries which is expected in early 2025 at the earliest. Table 3 provides information on the registers used.

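### The register comparison of randomised municipalities is fixed as difference-in-difference; adjusting for the pre-trial rate is generally more efficient and handles a chance baseline gap better

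*Protocol article*

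**What the plan says.** Study design announces the analysis: "Additionally, a register-based difference-in-difference study and a process-, realist- and health economic evaluation will be conducted as part of the trial". The section on the difference-in-difference design fixes the method: "Difference-in-difference analyses will be applied to estimate the difference in change in proportions breastfeeding at four months", and likewise for average weeks of breastfeeding. The contrast is the change from 2021 or earlier to 2022 or later, that is, before to after "the intervention period comparing the intervention and control arm". Data cover all dyads "in the included 21 municipalities from 2015 to 2025", and the effect of the intensified intervention is an interaction term in the same analysis. One reason for the method is given: "The advantage of this approach is that it will provide an estimate of the effect if treatment is upscaled to the entire country".

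The arms being compared were randomised: "The participating municipalities were randomised for either the intervention or control arm by a statistician using computer-generated cluster randomisation". The strata were region and annual births (below 900, or 900 and over); the pre-trial breastfeeding rate was not a stratum. On numbers, "Each of the 21 participating municipalities constitutes a cluster in the trial", and Table 2 refers to "210 health visitors from the 11 intervention municipalities", which leaves 10 controls.

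On status, the section on outcome measures says that the trial was designed around survey-based measures and treats other sources as supplementary. Table 3 nevertheless lists the National Child Health Register as a source for both outcomes under its Primary heading.

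**The concern.** Difference-in-difference earns its place when groups were not randomised and may differ systematically in level. Here the level difference between arms is chance. Part of a chance gap would close without any intervention if municipal rates move between periods or are measured with error. Subtracting all of it then removes too much, and the estimate leans against whichever arm happened to start higher. The efficient weight under randomisation is the slope of the post-period rate on the pre-period rate, which can be estimated from the same data.

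The stated reason does not favour difference-in-difference. Reach beyond the survey respondents comes from the register covering all births, and a baseline-adjusted comparison has the same coverage.

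At stake are the precision of the register estimates for the four-month proportion and average weeks, the matching estimate for the intensified intervention, and their sensitivity to a chance starting gap between 11 and 10 municipalities.

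**Working it through.** **The plan's own figure.** No precision figure is given for the register analysis. The survey sample size does reproduce: 49% v 56%, two-sided 5% (assumed) and 80% power need 798 mothers per arm. Solving 8m = 798 × (1 + (m − 1) × 0.001) gives m = 797.2 / 7.202 = 110.7, the plan's 111.

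**Inputs from the article.** 11 v 10 municipalities; base rate 49%; ICC 0.001; data from 2015, so 7 pre-trial years (2015-2021).

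**Assumed inputs.** Births: more than 6,000 families / 11 municipalities = 545 over the 18 months from April 2022 to October 2023, or 545 / 1.5 = 364 a year. That gives 7 × 364 = 2,548 births before and, with 2 post years assumed, 728 after. The between-period correlation r of true municipal rates is varied from 0.3 to 0.95, and the ICC from 0.001 to 0.02.

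**Formulas** (municipality level, with T = ICC × 0.49 × 0.51):
- V_pre = T + 0.2499 × (1 − ICC) / 2,548; V_post is the same with 728; C = r × T.
- Difference-in-difference: V_pre + V_post − 2C.
- Baseline-adjusted: V_post − C² / V_pre, times 1 + 1/17 for estimating the slope from 21 municipalities in two arms.
- Slope b = C / V_pre. Squared standard errors multiply by 1/11 + 1/10 = 0.1909.

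**At ICC 0.001 and r = 0.5:**
- T = 0.000250; V_pre = 0.000250 + 0.000098 = 0.000348; V_post = 0.000250 + 0.000343 = 0.000593; C = 0.000125; b = 0.36.
- Difference-in-difference: 0.000348 + 0.000593 − 0.000250 = 0.000691, SE 1.15 points.
- Baseline-adjusted: (0.000593 − 0.000045) × 1.059 = 0.000580, SE 1.05 points. Variance ratio 1.19.
- Post-period only: 0.000593, SE 1.06 points.
- If only the 545 trial-period births counted as post, V_post is 0.000707 and the ratio is 0.000805 / 0.000701 = 1.15.
- The SD of the chance gap is √(0.000348 × 0.1909) = 0.8 points. A 1-SD gap shifts difference-in-difference by (1 − 0.36) × 0.81 = 0.5 points.

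**Variance ratio, difference-in-difference to baseline-adjusted (slope estimated):**

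| ICC | r = 0.3 | 0.5 | 0.7 | 0.8 | 0.9 | 0.95 |
|---|---|---|---|---|---|---|
| 0.001 | 1.30 | 1.19 | 1.11 | 1.07 | 1.04 | 1.02 |
| 0.005 | 1.39 | 1.23 | 1.10 | 1.04 | 1.00 | 0.98 |
| 0.01 | 1.42 | 1.24 | 1.10 | 1.04 | 0.99 | 0.97 |
| 0.02 | 1.43 | 1.25 | 1.11 | 1.05 | 0.99 | 0.97 |

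A simulation of 40,000 allocations per cell agrees to about 0.01. Both estimators' mean errors were within 0.03 points of zero in every cell, so both are unbiased over randomisations.

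Difference-in-difference is also less precise than ignoring the baseline when b is below 0.5. At ICC 0.001 this means r below about 0.7.

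**How drift happens matters.** If each municipality has a stable level with independent yearly fluctuations, a 7-year average removes most of the noise. With 500 or 900 births a year, ICC 0.001-0.05 and half or more of the between-municipality variance stable, the ratio is about 0.95-1.04. If rates instead drift gradually (autoregressive by year, 364 births), it is 1.17-1.19 at year-to-year correlation 0.5, 1.08-1.12 at 0.8 and 1.01-1.07 at 0.9, because older years predict less.

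**The case against.** The strongest reply is that both estimators are valid and the choice between them is one of efficiency. Randomisation makes parallel trends hold in expectation, so a reader who infers that difference-in-difference is biased or improper here goes further than the documents allow. The over-correction exists only conditionally on the realised gap. This stands.

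The deciding correlation is not in the article. The Background reports that the four principles entered national recommendations and spread, partially or completely, through maternity wards. A uniform national change cancels in difference-in-difference; only uneven uptake lowers the correlation, and the article gives no size for that. This stands too. It is equally wrong to infer that baseline adjustment is never less precise: with very stable rates and 21 municipalities it can lose a few percent of variance.

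The practical effect at the plan's ICC is small. In the worked case the standard errors are 1.15 and 1.05 points against a 7-point target, so power is not in question. Quoting a shift of about 0.9 points is possible, but it needs an ICC of 0.005, five times the plan's value. Stratification by region and annual births should also limit chance gaps somewhat; the calculation above ignores it.

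Finally, the register analysis is supplementary and its model details may sit in an analysis plan not shown. That excuses missing covariates and variance methods. It does not remove the point, because the article itself names the estimator and gives a reason that does not distinguish it from the alternative.

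**Conclusion.** The point holds as a low-severity efficiency improvement. The article commits a randomised comparison to a baseline weight of 1 where an estimated weight is generally better. The variance cost is about 15-43% at between-period correlation 0.3-0.5, 4-11% at 0.7-0.8 and about nil at 0.9; at 0.95 difference-in-difference may be up to 3% better. At the plan's ICC and correlation 0.5, a 1-SD baseline gap moves the estimate by about 0.5 points.

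These figures rest on assumed births, 2 post years, an assumed range of correlations and unrestricted allocation. If the 7-year average mainly smooths independent yearly noise, the loss largely vanishes. The register estimate stays valid, and the survey primary analysis is untouched.

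**What to change.** In the section on the difference-in-difference design, and where Study design announces it, make the main register analysis a comparison of post-period outcomes between the randomised arms, adjusted for each municipality's own pre-period value of the same outcome with an estimated slope, and for the two randomisation strata. A mixed model on both periods with a common pre-period mean in the two arms is an alternative. Apply the same to average weeks. For the intensified-intervention interaction, adjust for the municipality's pre-period gap between the target group and other mothers. Keep difference-in-difference as a sensitivity analysis, and attribute the reach of the estimate to full register coverage.

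The cost is wording, on the same data extract, to be settled before the register outcomes are analysed. One degree of freedom goes to the slope and two to the strata as main effects. If municipal rates prove very stable, a few percent of variance may be lost.

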### Study population

The study setting includes 21 municipalities in Denmark, all of which are situated in the North Denmark Region (*n* = 6) or Region of Southern Denmark (*n* = 15) (see Fig. 1). Denmark consists of a total of five regions. The two selected regions have some of the highest proportions of mothers who are of young age and/or have a low educational attainment. Each of the 21 participating municipalities constitutes a cluster in the trial.

**Fig. 1 Fig1:**
[figure not shown]
Map of Denmark. Green areas indicate intervention clusters; blue areas, control clusters

#### Eligibility criteria

All women giving birth in the 21 municipalities during the project period from April 2022 to end of 2023 are eligible for inclusion in the trial provided they are: 1) ≥ 15 years old, 2) intend to breastfeed their infant, 3) were discharged from the hospital less than seven days after giving birth^1^, 4) gave birth to a singleton, and 5) had a term born child. The exclusion criteria are: 1) insufficient Danish and English language skills to respond to questionnaires and understand the support conveyed in either Danish or English, 2) known substance use disorder or use of illegal drugs, and/or 3) known morbidity or disablement affecting their ability to breastfeed. Fathers/partners are invited to participate based on their partner’s eligibility and must be able to understand Danish or English.

### Description of the intervention

#### Control group – care as usual

New families in the control clusters will receive standard care breastfeeding support. The Danish Health Authority provides guidance on what should be provided as standard care. Home visits are offered to all children and their families from birth to two years of age. Standard care is a minimum of five visits during the infant’s first year of life for a normal trajectory, with an option for provision of needs-based visits [28]. The aim of standard care is prevention and health promotion where relevant topics are covered depending on the timing of the visits [28]. Table 1 presents a description of standard care.

**Table 1 Tab1:** Description of standard care

**Visits**
The recommendation from the Danish Health Authority is that a minimum of five consultations (mostly home visits) are offered to all children and their families from birth to one year of age under the auspices of the municipality-based health visiting programme [28]:
1. First visit within the first week of life (for mothers discharged < 72 h postpartum)
2. Second visit during the first month of life
3. Third visit when the infant is two months old
4. Fourth visit when the infant is four to six months, and
5. Fifth visit when the infant is eight to ten months old
In the standard care lies an option for health visitors to offer families so called ‘needs based visits’ or follow-up if the health visitor considers this required [28]
**Content of the visits**
The content of the standard care is prevention and health promotion, and subjects depend on the timing of the visits [28] The topics include:
• Breastfeeding support and –cessation prevention
• Infant thriving
• Family formation
• Physical and mental condition of the infant, including infant-parent attachment
• Infant self-regulation
• Psychomotor development
• Parents’ mental well-being (including screening for postpartum depression)
• Infants’ eating- and sleeping patterns
• Introduction to solid foods (4–6-month visit)
• Language development, and
• Prevention of accidents

#### Intervention group

In the intervention arm, the intervention is implemented into the already existing health visiting programme. All new parents in the intervention clusters will thus receive strengthened breastfeeding support if they accept the health visiting programme. The four key principles from the original 2013–2014 intervention at hospitals are adapted to the municipality setting. Consequently, the current intervention seeks to strengthen consistency in breastfeeding support across sectors and thus to reduce any confusion among parents. The core of the intervention is building a trustful relation between health visitors and families and that the health visitors strengthen parents’ action competency. The intervention builds on theories of tailored communication and support [39, 40] and breastfeeding self-efficacy [41, 42]. The activities generating strengthened support are competence training for health visitors and development of new health education materials targeting the parents. The provision of pregnancy visits will underpin trustful relationship building between the family and the health visitor. The duration and form of the training and the contents of the intervention are presented in more detail in Table 2.

**Table 2 Tab2:** Description of the intervention programme

**Development and implementation**
For the adaptation of the previous successful breastfeeding intervention done by Nilsson and colleagues (2017) in hospital setting, an assessment of the needs of families following discharge from hospital after birth and until six months postpartum was carried out. Programme objectives corresponding to findings from the needs assessment formed the basis of the adaptation. In the adaptation process, a participatory approach including health visitor representatives from each of the intervention municipalities was chosen to enhance ownership, to match the organisational structure of the setting (the Danish Health visiting programme), and to ensure implementation in the intervention municipalities. The final intervention programme consisted of a breastfeeding programme for parents and a related training programme for health visitors. In December 2021, 210 health visitors from the 11 intervention municipalities completed a preparatory 3.5-h e-learning course, and in March 2022 they participated in the 15-h physical attendance interactive training programme supported by a written manual. Following training, the health visitors immediately initiated implementation of the programme in their municipalities
